### Sample size and recruitment

The literature reports a mean 3-year disease-free survival rate of 75–85% for the sample to be included in the study [16]. For patients with mid-rectal tumors (cT2N+ and cT3N0) without high risk MRI findings, the 3-year disease-free survival rate was estimated to be 80% for both direct TME and TME following neoadjuvant chemoradiotherapy. Under these conditions, with α = 0.05 (95% confidence interval) and 80% power, the power analysis indicated that a total of 396 patients (1:1 ratio) would be required. Considering a 10% dropout rate, it is planned to include 218 patients in each group, for a total of 436 patients.

According to data from the Turkish Ministry of Health, General Directorate of Public Health, a total of 24,312 patients were diagnosed with rectal cancer between 2020 and 2024, of whom 17,896 underwent surgery (https://hsgm.saglik.gov.tr/tr/kanser.html). Since this study will be conducted nationally under the sponsorship of the main society of Turkish colorectal surgeons TSCRS, we anticipate reaching the targeted patient number within five years from the start of the study. To achieve this goal, TSCRS will utilize various channels, including mailing, social media, and its website, to announce the study and inform surgeons about the protocol.

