### Statistical methods

During the study, missing data analyses and data quality assessments will be actively conducted, and measures to prevent data loss and enhance data quality will be implemented as appropriate. All statistical analyses will be conducted by experts from the TSCRS Biostatistics and Bioinformatics Analysis Unit using SPSS (SPSS Inc, Chicago, IL) software packages.

Multivariable regression analyses will be conducted to evaluate the effect of treatment strategy (direct TME vs. nCRT followed by TME) on the primary and secondary outcomes. The following covariates will be included in the models based on clinical relevance and literature review: age, sex, clinical T stage (cT2 vs. cT3), clinical N stage (N0 vs. N+), tumor differentiation, regimens of neoadjuvant treatment (long-course CRT, short-course RT, TNT with long or short-course RT), interval between neoadjuvant RT/CT and surgery, comorbidities (e.g., Charlson Comorbidity Index), performance status, postoperative complications (Clavien-Dindo), tumor histology, pathologic TME quality (pathologic completeness of the mesorectum), and center effect (as a random effect if appropriate).

For time-to-event outcomes such as disease-free survival (DFS) and overall survival (OS), Cox proportional hazards regression models will be used to estimate hazard ratios and 95% confidence intervals. The proportional hazards assumption will be tested using Schoenfeld residuals.

To address potential selection bias due to the non-randomized design, propensity score methods will be applied. Specifically, propensity scores for receipt of nCRT (vs. direct TME) will be estimated using logistic regression including the aforementioned covariates. The primary analysis will adjust for the propensity score as a covariate in the Cox model. Sensitivity analyses will be conducted using propensity score matching (1:1 nearest neighbor matching without replacement) and inverse probability of treatment weighting (IPTW) to ensure the robustness of results.

Patients lacking the main data specified in the inclusion and exclusion criteria, demographic data, or follow-up data related to the primary endpoint will be completely excluded from the study. Patients with missing data from other variables or secondary endpoints will only be excluded from those specific analyses, and secondary endpoints will be evaluated using data from patients with complete datasets.

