#### Adverse event reporting, safety and criteria for discontinuing.

In this study, a non-standard treatment that is not currently implemented will not be evaluated. Consequently, side effects and adverse events will be documented as part of the routine monitoring process. However, the steering committee (TB, AEC) will assess interim analyses regarding any safety measures every six months. The study will be terminated if a new treatment relevant to patient groups in rectal cancer management is introduced during the study period and included in the guidelines, and/or there are unacceptable disease-free survival or local recurrence rates (a difference of more than 10%) in any treatment arm that could adversely affect the success of the project. To ensure the safe conduct of the project in the event of such risks, measures will be taken and monitored by the steering committee. The TSCRS will inform relevant parties and all members through e-mail, society website and social media accounts regarding important protocol amendments.

The study will continue until the necessary number of patients is reached. The study will be terminated if a new treatment relevant to patient groups in rectal cancer management is introduced during the study period and included in the guidelines, and/or there are unacceptable disease-free survival or local recurrence rates (a difference of more than 10%) in any treatment arm.

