## Discussion

In line with current recommendations, some surgeons perform upfront TME for patients with T2-3 node-positive mid-rectal cancer in the absence of MRF involvement. However, in these cases, the common approach is to administer neoadjuvant chemoradiotherapy. This study seeks to evaluate whether upfront TME achieves non-inferior 3-year disease-free survival compared to the standard.

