### Limitations

The non-randomized, observational design introduces the potential for selection bias. Although propensity score methods will be used to minimize selection bias, residual confounding may persist. Our study is expected to span at least five years, which presents logistical challenges both in terms of patient recruitment and follow-up. By the end of this period, the relevance and generalizability of the results may be limited due to potential changes in clinical practice and evolving treatment standards.

Moreover, the trial’s reliance on MRI-based risk stratification may lead to variability in interpretations across different centers, particularly in the absence of centralized imaging review. Another limitation is the absence of central pathology review, which may impact the consistency of histopathological assessments. To minimize these limitations, standard MRI and pathology assessments have been published on the study website. Additionally, standardized MRI and pathology evaluation protocols were presented during a webinar organized for candidate participating centers. Furthermore, the TSCRS commits to providing central review and support in cases where centers require assistance with MDT, MRI, or pathology evaluations.

Unfortunately, MSI testing is not yet performed as a standard procedure in endoscopic pathology in Türkiye. Many centers offer it only as an additional test, which is time-consuming, often not covered by insurance, and results in extra costs for patients. Therefore, MSI is tested in endoscopic pathology only if it is routinely performed at the center or if the patient consents to undergo testing at another institution at an additional cost. For this reason, we could not specify unknown pre-treatment MSI status as an exclusion criterion. However, MSI testing is routinely performed in final surgical pathology in our country. Patients found to have MSI positivity in surgical pathology will not be included in the final analysis. Similarly, patients who underwent preoperative MSI testing (if performed), were found positive, and/or received immunotherapy will also be excluded from the final analysis.

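### The primary analysis and both sensitivity analyses use one propensity score from the same measured covariates, so their agreement cannot show robustness to the residual confounding the protocol concedes

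*Protocol article*

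**What the plan says.** Under Statistical methods, the protocol article lists covariates and then states that "propensity scores for receipt of nCRT (vs. direct TME) will be estimated using logistic regression including the aforementioned covariates". The primary analysis enters that score as a covariate in a Cox model. Two sensitivity analyses follow: 1:1 nearest-neighbour matching and "inverse probability of treatment weighting (IPTW) to ensure the robustness of results". No other sensitivity analysis for confounding is described.

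Under Limitations: "Although propensity score methods will be used to minimize selection bias, residual confounding may persist". The Discussion gives the aim: "This study seeks to evaluate whether upfront TME achieves non-inferior 3-year disease-free survival compared to the standard".

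No non-inferiority margin is stated as such. The nearest figure is in the discontinuation criteria: "there are unacceptable disease-free survival or local recurrence rates (a difference of more than 10%) in any treatment arm".

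**The concern.** The three analyses differ in how the score is used (regression, matching, weighting) but share one assumption: nothing important to both treatment choice and recurrence is missing from the covariate list. If something is missing, all three are biased in the same direction by nearly the same amount. Their agreement is then expected whether or not the assumption holds, so it cannot count as evidence for it. The stated purpose credits the set with more than it can deliver, and nothing described in the article addresses the problem that the Limitations section accepts.

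This matters most for a non-inferiority conclusion in a non-randomised study. If patients with a better prognosis tend to go straight to surgery, the bias favours the conclusion being sought. Three matching hazard ratios could then be reported as a robust result.

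Such a factor is plausible. The Introduction says the European guideline directs upfront surgery by cT3 sub-stage and position relative to the levators. The covariate list has only cT2 vs cT3 and N0 vs N+, with no cT3 sub-stage and no tumour height.

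**Working it through.** **Inputs from Sample size and recruitment.** The assumed 3-year DFS is 80% in each group, and an allowance of 10% for dropout raises the target to 218 per group (436). The power statement reads: "with α = 0.05 (95% confidence interval) and 80% power, the power analysis indicated that a total of 396 patients (1:1 ratio) would be required". Neither the margin nor the sidedness of α is given.

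**Reproducing the sample size.** With a 10-point margin, one-sided α = 0.05 and 80% power:

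n per group = (1.645 + 0.842)² × (0.8×0.2 + 0.8×0.2) / 0.10² = 197.8, so 198, and 396 in total. This matches. 198 × 1.10 = 217.8, so 218 per group and 436 in total. One-sided 0.025 would give 504. The 10-point margin and one-sided 5% are therefore inferred from the fit to 396; 10% also appears in the discontinuation criteria.

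**Margin as a hazard ratio.** ln(0.70)/ln(0.80) = 1.598.

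**Do the three uses of the score move together?** Simulation of 396 patients per trial, 400 replicates, true 3-year DFS 80% (nCRT) vs 70% (direct TME). One logistic score was fitted on six measured baseline covariates, and a binary factor U was left out of it. Matching used an assumed caliper of 0.2 SD. The strength of U is an assumption.

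| U: OR for nCRT, HR for DFS event | U in nCRT / direct TME | Mean HR: covariate / matching / IPTW | All three meet the margin |
|---|---|---|---|
| OR 1, HR 3 (no confounding) | 40% / 40% | 1.59 / 1.58 / 1.59 | 3% |
| OR 2, HR 2 | 47% / 32% | 1.45 / 1.44 / 1.44 | 10% |
| OR 3, HR 3 | 52% / 28% | 1.21 / 1.21 / 1.21 | 33% |
| OR 4, HR 4 | 55% / 25% | 1.04 / 1.03 / 1.04 | 67% |

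The covariate and matched estimates differed by a ratio above 1.25 in only 1% to 3% of trials, with or without confounding by U. Agreement is as common when the answer is wrong as when it is right.

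**Illustrative factor: HR 2, about 57% of nCRT vs 33% of direct TME.**

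- Bias factor = (1 + 0.57×(2−1)) / (1 + 0.33×(2−1)) = 1.57/1.33 = 1.18. Apparent HR = 1.60/1.18 = 1.36. Separate simulations with a factor of about this strength gave 1.30 to 1.35 for each use of the score that was run.
- Log-HR scale, the scale of the planned Cox model: events 396 × 0.20 = 79; SE = 2/√79 = 0.225. Non-inferiority requires log HR + 1.645×0.225 < ln(1.598) = 0.469, so log HR < 0.099.
 - Apparent HR 1.60: z = (0.099 − 0.469)/0.225 = −1.645, giving 5%.
 - Apparent HR 1.35: z = (0.099 − 0.300)/0.225 = −0.89, giving 19%.
 - Apparent HR 1.30: z = (0.099 − 0.262)/0.225 = −0.73, giving 23%.
- Difference in proportions, 198 per group:
 - HR 1.35 gives DFS 0.80^1.35 = 0.740, loss 0.060, SE 0.0422; z = 0.040/0.0422 − 1.645 = −0.70, giving 24%.
 - HR 1.30 gives DFS 0.748, loss 0.052, SE 0.0419; z = 0.048/0.0419 − 1.645 = −0.50, giving 31%.

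**How little would overturn the expected result?** At an observed HR of 1.0 the one-sided upper limit is exp(1.645×0.225) = 1.447. The gap to the margin is 1.598/1.447 = 1.104. E-value = 1.104 + √(1.104×0.104) = 1.44.

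**The score as literally listed.** The covariates include neoadjuvant regimen and the interval from neoadjuvant treatment to surgery, which exist only in the nCRT group. Adding regimen indicators in a simulated data set gave complete separation, with fitted scores of about 1 and about 0. The Cox model with the score could not be estimated, no pairs matched, and every IPTW weight was 1.0, which is a crude comparison.

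**The case against.** Several counter-arguments have force.

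- **The detail may sit in an SAP.** Quantitative bias analysis is often placed there, and none is shown. This stands: the absence of an E-value is not in itself the fault. What remains is the purpose the article gives to matching and IPTW, which they cannot serve for the main threat.
- **The limitation is disclosed, and robustness could mean robustness to the adjustment method.** That reading is possible, but the text does not say so. A reader of three concordant results would take more from it.
- **Eligibility already restricts risk.** MRF involvement, EMVI, pathological lateral nodes, cT4 and obstruction are excluded. This makes a very strong residual factor less likely, but does not remove factors outside the covariate list.

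A reader might infer three stronger things that the document does not support. First, that the three analyses are bound to agree: with the score as listed they fail in different ways, and even with a usable score they target somewhat different effects. Second, that they would conceal an entire margin-sized loss: in the simulation that took about OR 4 with HR 4, and weaker factors conceal only part. Third, that the protocol admits surgeons pick better tumours for direct TME: the Limitations section names selection bias and residual confounding, but gives no mechanism and no direction.

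**Conclusion.** The point holds in a limited form. Matching and IPTW test sensitivity to how one score is used. They do not test sensitivity to what the score omits, so the stated claim of robustness is too strong.

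For a factor of HR 2 at about 57% vs 33%, a true HR of 1.6 would appear as about 1.30 to 1.35. False non-inferiority would rise from 5% to about 20% on the log-HR scale, or about 24% to 31% as a difference in proportions. These sizes depend on an assumed strength, prevalence and direction of the factor, on an inferred 10-point margin and one-sided 5% level, and on a score restricted to baseline covariates. The structural conclusion, that agreement among the three is uninformative about an omitted factor, depends on none of the assumed sizes; it needs only a score that can be fitted. The matter should be corrected before analysis. It does not invalidate the study.

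**What to change.** In Statistical methods:

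1. Limit the propensity score to covariates known before treatment starts. Regimen and interval to surgery must leave the score because they separate the groups. Postoperative complications and TME quality also arise after the treatment choice and fall outside a pre-treatment list.
2. Describe matching and IPTW as checks of the adjustment method, and remove the claim that they secure robustness.
3. State the non-inferiority margin explicitly.
4. Add one bias analysis of the primary result against that margin: either the E-value for the confidence limit, or a tipping-point grid over confounder prevalence by group and hazard ratio.
5. Report, as context and not as a pass/fail rule, how far the estimate moves when a strong measured factor such as clinical N stage is dropped from the score.

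The cost is a few sentences and a short calculation on the fitted model, with no new patients or data. The downside is that a borderline result may have to be reported as sensitive to unmeasured confounding.

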#### Exclusion criteria.

cT4 tumors assessed by MRIStage IV disease assessed by MRI and/or CTPatients with MSI (+) in TME pathologyPatients who received neoadjuvant immunotherapyEmergency surgeryClinical obstructionPrevious pelvic radiotherapyPatients treated without a multidisciplinary council decisionInflammatory bowel diseases (Crohn’s disease, Ulcerative colitis)Familial adenomatous polyposis (FAP), attenuated FAP, and other polyposis syndromesHereditary non-polyposis colorectal cancer (Lynch syndrome)Synchronous colon tumors

Patients undergoing surgeries other than TME (e.g., partial mesorectal excision, rectosigmoid resection, end colostomy) will not be included in the study. Following data entry, patients for whom pathology reports indicate that TME was not performed or who has missing data regarding inclusion criteria will be excluded from the study. Patients who are unable to complete neoadjuvant therapy for any reason (such as toxicity, non-compliance, or accessibility issues) will not be excluded from the study. These patients will be evaluated within the neoadjuvant therapy group. Accordingly, when analyzing this aspect, an intention-to-treat analysis will be conducted without cross-over.

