### Outcomes

#### Primary outcome measure.

3-year DFS: The proportion of patients who remain free of disease recurrence (local or distant) three years after surgical intervention. DFS will be assessed through clinical evaluations, imaging studies, and pathology reports at regular follow-up intervals.

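### The missing-data rule, read as written, deletes event-free patients lost before 3 years instead of censoring them, and three sections disagree on whether a missing MSI result also means deletion

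*Protocol article*

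**What the plan says.** The deletion rule is in the Statistical methods section of the protocol article. It begins "Patients lacking the main data specified in the inclusion and exclusion criteria, demographic data" and ends "or follow-up data related to the primary endpoint will be completely excluded from the study". The next sentence treats other missing variables more mildly: those patients drop out only of the analyses concerned.

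The Primary outcome measure section defines 3-year DFS as "The proportion of patients who remain free of disease recurrence (local or distant) three years after surgical intervention". Statistical methods nevertheless treats DFS as a time-to-event outcome, for which "Cox proportional hazards regression models will be used to estimate hazard ratios and 95% confidence intervals", and makes the propensity-adjusted Cox model the primary analysis.

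On missing eligibility data, the Exclusion criteria section is narrower than Statistical methods. It removes a patient "who has missing data regarding inclusion criteria will be excluded from the study" and does not mention missing exclusion-criteria data. MSI positivity in the TME specimen is an exclusion criterion. The Limitations section explains that MSI is not tested as standard on the endoscopic biopsy, relies on the statement that "MSI testing is routinely performed in final surgical pathology in our country", and removes from the final analysis patients found MSI-positive or given immunotherapy. It does not say what happens when no MSI result can be obtained.

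**The concern.** **Follow-up.** A patient who recurs at 20 months has a known 3-year status. A patient who is event-free at 20 months and then lost does not. A rule that deletes patients without endpoint data, applied to an endpoint defined as a 3-year proportion, removes the second and keeps the first. Membership of the analysis set then depends on outcome, and adjustment for baseline covariates or a propensity score cannot undo that. A Cox model would keep the second patient's 20 months at risk, so the deletion is unnecessary. If loss differs between groups, the group with more loss looks worse than it is. Differential loss is possible here: treatment is not randomized, and the Follow-up section accepts that follow-up protocols may vary between centers.

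**MSI.** If missing exclusion-criteria data lead to deletion, an nCRT patient with no residual tumour in the specimen and no biopsy result could be removed for lack of an MSI result. Such patients arise from nCRT and are likely to have a good prognosis, so their removal would lower DFS in the nCRT group and favour direct TME.

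**Working it through.** **Inputs from the protocol article (Sample size and recruitment).** "the 3-year disease-free survival rate was estimated to be 80% for both direct TME and TME following neoadjuvant chemoradiotherapy"; 396 patients before dropout; 10% dropout; 218 per group, 436 in total.

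**The plan's own dropout figure.** 396 / 2 = 198 per group; 198 × 1.10 = 217.8, rounded up to 218; 2 × 218 = 436. This matches. Dropouts are added on top of the required number, which fits the reading that they contribute nothing to the analysis.

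**Step 1: deletion of event-free losses.** Assumptions: exponential DFS with S(3) = 0.80; a fraction L of patients is lost at a time uniform on 0 to 3 years, independently of recurrence; a recurrence before loss is observed and kept.

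- Mean of S(t) over 0 to 3 years: (1 − 0.80) / (−ln 0.80) = 0.20 / 0.2231 = 0.896.
- Share of patients deleted: 0.896 × L.
- Apparent 3-year DFS: 0.80(1 − L) / (1 − 0.896 L).

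| Loss L | Share deleted | Apparent DFS | Shift from 80% |
|---|---|---|---|
| 5% | 4.5% | 0.760 / 0.955 = 79.6% | −0.4 points |
| 10% (planned) | 9.0% | 0.720 / 0.910 = 79.1% | −0.9 points |
| 20% | 17.9% | 0.640 / 0.821 = 78.0% | −2.0 points |

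Check with exponential instead of uniform loss: 79.57%, 79.10% and 78.05%, so the form of the loss distribution matters little.

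**Step 2: effect on the comparison.** With the same loss in both groups and the same true DFS, both estimates shift equally and the difference is unaffected. With 5% against 20% loss (assumed) and 80% true DFS in both, the spurious gap is 79.57 − 77.98 = 1.6 points (1.5 with exponential loss).

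**Step 3: the alternatives.** If the same patients are censored at last assessment and censoring is non-informative, the expected estimate stays at 80%. If the rule means only patients with no follow-up at all, deletion does not depend on an observed outcome. Those patients would contribute no time at risk to a Cox model either, so the bias is small.

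**Step 4: the MSI route.** The article gives no complete-response rate and no DFS for such patients, so both are assumed. If a fraction p of the nCRT group are complete responders with 3-year DFS s, overall DFS is 80% and all of them are deleted, the rest have DFS (0.80 − p·s) / (1 − p).

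| p | s | Remaining nCRT DFS | Shift | Deleted of 218 |
|---|---|---|---|---|
| 10% | 90% | 0.710 / 0.90 = 78.9% | −1.1 points | about 22 |
| 10% | 95% | 0.705 / 0.90 = 78.3% | −1.7 points | about 22 |
| 25% | 90% | 0.575 / 0.75 = 76.7% | −3.3 points | about 54 |
| 25% | 95% | 0.5625 / 0.75 = 75.0% | −5.0 points | about 54 |

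These are upper figures for each pair of assumptions, because any responder with a biopsy MSI result would stay.

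**The case against.** The rule speaks of patients lacking follow-up data, not of patients followed for less than 3 years. Under a Cox model, a patient seen at 18 months does have endpoint follow-up, so the authors may mean only patients never seen again. This reading is open. The 3-year-proportion definition and the dropout allowance point the other way, and the text does not settle the matter.

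It is also fair that the shift at the planned dropout is under one point and largely cancels in the comparison, and that the article promises missing-data analyses, loss-prevention measures and weekly completeness checks. These reduce the amount of loss. They do not change what is done with patients who are lost.

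On MSI, a reader might infer that the plan will delete the best nCRT responders, and only them. The article does not establish this. The main data are not defined, the Exclusion criteria section confines the rule to inclusion criteria, and Limitations removes only MSI-positive or immunotherapy-treated patients and declines to make unknown pre-treatment MSI an exclusion criterion. A biopsy result would avoid deletion, and a direct-TME patient without an MSI result would fall under the same literal rule.

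Two further inferences should be resisted. Recruitment and study completion are both given as August 2030, so one might project mass deletion of patients with short follow-up. That is a separate calendar conflict, to be resolved on its own terms. Nor can the shifts be measured against a non-inferiority margin: none is stated, and the 10% difference in the discontinuation criteria is a termination threshold.

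Finally, excluding patients whose eligibility cannot be confirmed is conventional and is not criticised here.

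**Conclusion.** The point stands in limited form. The follow-up rule, combined with the endpoint definition, makes inclusion in the analysis depend on outcome and withholds from the Cox model data it is built to use. The size is modest: about 0.9 points on an 80% DFS at 10% loss, little in the comparison if loss is equal, and about 1.6 points if loss is 5% against 20%. This rests on exponential DFS, independent loss and the reading that event-free patients lost before 3 years lack endpoint data.

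The MSI consequence is a possibility arising from three sections that do not agree. Its size, 1.1 to 5.0 points against nCRT, rests wholly on assumed complete-response rates of 10–25%, assumed DFS of 90–95% in those patients, and deletion of all of them. The disagreement between the sections needs correcting whatever the size. This goes beyond detail that could be left to an analysis plan, because the article states a rule and that rule should be replaced.

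**What to change.** 1. In Statistical methods, replace deletion for missing primary-endpoint follow-up with censoring at the last disease assessment, in both Kaplan-Meier and Cox analyses, keeping all patients with confirmed eligibility.
2. Reconcile Exclusion criteria, Statistical methods and Limitations on missing eligibility data, and state that an unavailable MSI result is not in itself a reason for exclusion from the analysis in either group.
3. Add a sensitivity analysis by MSI-known status.

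The cost is rewording and modest extra analysis, with no new data collection. A few patients of unknown status who are in fact MSI-positive may be retained, which the sensitivity analysis addresses. The change is best made before outcomes accrue.

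### The stated rule for missing covariates makes the primary propensity-adjusted Cox analysis a complete-case analysis, with no allowance for that loss in the sample size and a possible, not certain, bias

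*Protocol article*

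**What the plan says.** Three statements in the Statistical methods section act together.

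- The score: "propensity scores for receipt of nCRT (vs. direct TME) will be estimated using logistic regression including the aforementioned covariates". The list covers age, sex, clinical T and N stage, differentiation, neoadjuvant regimen and interval to surgery, comorbidity, performance status, postoperative complications, histology, TME quality and centre.
- The primary model: "The primary analysis will adjust for the propensity score as a covariate in the Cox model". Matching and inverse probability weighting on the same score are the sensitivity analyses.
- The rule for missing values outside the core data: "Patients with missing data from other variables or secondary endpoints will only be excluded from those specific analyses". No imputation is mentioned.

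A separate, stricter rule says that patients lacking eligibility data, demographic data or "follow-up data related to the primary endpoint will be completely excluded from the study".

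On numbers, Sample size and recruitment asks for 396 patients in a 1:1 ratio and then states: "Considering a 10% dropout rate, it is planned to include 218 patients in each group, for a total of 436 patients". It does not define dropout and does not mention loss through missing covariates.

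**The concern.** A propensity score from an ordinary logistic regression cannot be computed for a patient with a missing predictor. Under the quoted rule, one blank field therefore removes a patient whose recurrence status is fully known. Matching and weighting need the same score and lose the same patients, so neither planned sensitivity analysis can show what the exclusion did.

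Age and sex (demographic data) and clinical T and N stage (eligibility data) fall under the stricter rule. Among pre-treatment covariates that leaves differentiation, histology, comorbidity and performance status exposed.

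Two things are at stake. The first is precision: observed events are discarded in a study whose purpose is to show that omitting neoadjuvant treatment does not worsen DFS. The second is validity: the primary comparison then describes fully documented patients, who may differ from the eligible population.

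**Working it through.** **Inputs from the protocol (Sample size and recruitment).** DFS: "the 3-year disease-free survival rate was estimated to be 80% for both direct TME and TME following neoadjuvant chemoradiotherapy". Error rates: "with α = 0.05 (95% confidence interval) and 80% power". Required 396, enrolled 436, dropout 10%.

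**Reproducing the plan's figure.** No margin or sidedness is given there. A non-inferiority comparison of 80% with 80%, with a 10-point margin and one-sided alpha 0.05, gives

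n per group = (1.645 + 0.842)² × (0.16 + 0.16) / 0.10² ≈ 198, or 396 in total.

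This matches exactly. The margin and sidedness are inferred: 10% is the only difference the protocol names, in its discontinuation criteria. One-sided 0.025 would give 504. The enrolment figure is 396 × 1.10 = 435.6, rounded to 436.

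**Room for further loss.** 436 × 0.90 = 392.4, so about 392 remain, already below 396. If there were no dropout at all, the allowance would be 436 − 396 = 40 patients, or 9.2%.

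**Share lost through covariates.** The rates are assumptions; the protocol gives none. With a fraction m missing in each of k = 4 fields:

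- all gaps in the same patients: loss = m
- independent gaps: loss = 1 − (1 − m)⁴

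The half-width of the unadjusted 95% interval for the 3-year difference, with N analysed patients split evenly, is 1.96 × √(0.16/(N/2) + 0.16/(N/2)). Power uses the inferred margin and alpha: Φ(0.10/SE − 1.645).

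| Assumption | Lost | Analysed, from 392 | Half-width (points) | Power |
|---|---|---|---|---|
| No covariate loss | 0% | 392 | 7.9 | 79.7% |
| 2% each, overlapping | 2% | 384 | 8.0 | 79% |
| 2% each, independent | 7.8% | 362 | 8.2 | 77% |
| 5% each, overlapping | 5% | 372 | 8.1 | 78% |
| 5% each, independent | 18.5% | 319 | 8.8 | 72% |

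In the last row, expected 3-year events at 80% DFS fall from 392 × 0.20 ≈ 78 to 319 × 0.20 ≈ 64, and the variance rises by 392/319 − 1 ≈ 23%.

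**A narrower count.** If pathology reports supply histology and differentiation almost completely, only comorbidity and performance status matter. At 5% each, independent, the loss is 1 − 0.95² = 9.75%. That leaves about 354 patients and a half-width of 8.3 points.

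**Bias.** No figure can be derived from the protocol. If missingness depends only on treatment, centre and other covariates that the model adjusts for, complete-case deletion does not by itself bias the treatment coefficient. Bias needs missingness that is still related to DFS after that adjustment.

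**The case against.** The strongest defence has five parts.

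1. **The sentence does not name the primary analysis.** It speaks of other variables and secondary endpoints. That is true, but the score needs every listed covariate and no other handling is given, so exclusion is the plain result of the text. It is also a stated rule: an analysis plan that imputed these values would contradict it.

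2. **Missingness may be low.** Data are entered prospectively and reviewed (Data collection and management), completeness is checked weekly (The data monitoring committee and interim analyses), and prevention measures are promised (Statistical methods). Eligibility and MSI status already depend on pathology. This bears on the rates and is why the range starts low. It does not say what happens to patients who remain incomplete.

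3. **The 10% may be meant to cover every unanalysable patient.** Dropout is undefined, so this stands. The shortfall from covariates is additional only if the 10% refers to other losses.

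4. **A reader might infer that the comparison will be biased**, because recording quality, treatment choice and outcome all vary by centre. The protocol does not support that as a conclusion. Centre is itself a listed covariate (as a random effect if appropriate), and nothing shows that missingness relates to outcome beyond the adjusted variables.

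5. **A reader might also count complications, TME quality, regimen and interval**, and infer a far larger loss, even of the whole direct TME group, in which regimen and interval have no value ("regimens of neoadjuvant treatment (long-course CRT, short-course RT, TNT with long or short-course RT), interval between neoadjuvant RT/CT and surgery"). Placing such variables in a treatment propensity score is a separate specification problem. Correcting it removes that loss, so it does not measure the effect of the missing-data rule.

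**Conclusion.** The point holds in limited form. As written, a missing baseline covariate removes a patient with observed DFS from the primary model and from both score-based sensitivity analyses. Under the assumed 2% to 5% missing in four fields, the loss runs from about 2% to 18.5%. At the upper end about 319 of 392 patients remain and the half-width grows from 7.9 to 8.8 points; at the lower end the effect is slight. These figures rest on assumed missingness, an even split between groups and an unadjusted approximation. The power figures also rest on the inferred margin and alpha. Precision falls below plan for any loss beyond the 10%, unless that figure was meant to include it. Bias is a possibility to guard against, not a demonstrated result. The change is worth making, but the rule does not by itself invalidate the study.

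**What to change.** For the primary analysis, replace exclusion for missing baseline (pre-treatment) covariates with multiple imputation. The imputation model should include treatment group, centre, the DFS event indicator and the cumulative baseline hazard. Estimate the propensity score and fit the Cox model within each imputed dataset, and combine the estimates with Rubin's rules. Keep the complete-case analysis as a sensitivity analysis, and report missingness per covariate by group.

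Patients otherwise retained under the Statistical methods section then stay in the primary analysis. This does not retain every eligible patient: the separate exclusion for missing eligibility, demographic or primary-endpoint follow-up data is unchanged.

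The cost is a revised sentence and modest extra analysis work, with no new patients or data. The price is reliance on a missing-at-random assumption. Retaining the present rule would instead call for more patients: if 5% lacked at least one covariate on top of 10% dropout, 396 / (0.90 × 0.95) = 463.2, or about 464 enrolled. The article states that recruitment had not begun, so the rule could be changed before any outcome was seen.
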